### Rehabilitation program

The research was conducted in a single center at an altitude of 1,600 m in the Bernese Swiss Alps in Crans-Montana, Switzerland. All participants were exposed to supervised exercise therapy as follows: eight to twelve 30-min-sessions per week of physical activity, of which 4–5 sessions were aerobic exercises in a pool, on a cycloergometer, treadmill or outdoor moderate intensity walking, 2–3 sessions of muscle strengthening through resistance and stretching exercises, 2–4 sessions of occupational activity, proprioceptive and range of motion exercises supervised by blinded certified therapists. Exercise intensity was determined according to the rate of perceived exertion measured using the Borg category ratio (CR-10) as previously described (37, 38). Intensity was increased progressively according to the patient's tolerance. In addition, 30-min sessions of auxiliary non-physical activity with a dietician, psychologist, acupuncturist, art therapist or social worker were planned as needed.

For the PUSH study, participant motivation and participation were measured based on the session reports of blinded therapist during weekly interdisciplinary meetings using the Pittsburgh rehabilitation participation scale as previously described (39).

### Outcome measures: Assessment, blinding, and rationale

The PUSH assessed objective and subjective outcomes of physical performance in addition to hemodynamic, cardiorespiratory, and cardiometabolic risk variables. Outcome assessments were done upon admission (baseline), facultatively at week 2 and at week 4 (Table 1). All participants, direct care providers and assessors were masked to the outcomes under investigation throughout the study. Whereas, participant and care providers were blinded by categorically withholding supplementary information on the glycemic control categories described above and exposures under investigation, main outcome assessors (therapists and laboratory technicians) were masked by complete prohibition of access to patient medication data as per previously established institutional policy.

**Table 1 T1:** Assessment time plan.

**Assessment**	**Time points during study**		
	**Baseline** ^a^	**Week 2**	**Week 4**
Screening for inclusion and exclusion criteria	°		
Participant characteristics^b^	°		
Status of medications^c^	°	°	°
Anthropometric and clinical parameters^d^	°	°	°
Laboratory tests^e^	°	°	°
Rehabilitation outcomes^f^	°	°	°
Transthoracic echocardiography^g^	°		°
Sonographic assessment of liver parenchyma (NAFLD)^h^	°		°
Muscle sonography^i^	°	°	°
Monitoring for adverse events^j^	Throughout stay		

a *Baseline was defined as the date of eligibility confirmation and inclusion in the study. If no data were available at baseline, the most recent data from the hospitalization prior to admission were used*.

b
*Included information on age, sex, medical history, complications and comorbidities, smoker status, coffee consumption.*

c
*Included antidiabetic agents, antihypertensives, lipid-lowering drugs, thrombocyte aggregation inhibitors, therapeutic anticoagulation, use of proton pump inhibitors, uric acid lowering drugs, antidepressants, opiates, NSAIDs, neuropathic pain treatment, vitamin D, iron, calcium, and magnesium substitution.*

d
*Included body weight, BMI, waist and hip circumferences, estimation of skeletal muscle mass in kg using the Baumgartner equation, mean systolic and diastolic blood pressures, mean fasting plasma glucose (for all groups at baseline, for group I and II at week 2 and 4), peak expiratory flow rate, state of nocturia, pain numeric rating scale [NRS] (range 1–10).*

e
*Included hemoglobin, thrombocyte count, magnesium, ionized calcium, ferritin, transferrin saturation, albumin, lipid profile (total cholesterol in mmol/L, mean HDL-Cholesterol in mmol/L, mean LDL-cholesterol in mmol/L, mean triglyceride in mmol/L), uric acid, NT-proBNP, kidney and liver parameters, CRP, vitamin D, TSH levels. HbA_1c_ testing was routinely done only upon admission (baseline).*

f
*Included 6-Minute Test Walk Distance (6-MWD), percent of predicted 6-MWD, Borg Rate of perceived exertion 1–10, saturation and heart rate after 6-Min walk test; functional independence measure (FIM), use of walking aids. Baseline and week 4 only: hand grip strength, state, and severity of general, physical (motor), and cognitive fatigue.*

g
*Included left ventricular mass index (LVMI), left atrial volume index (LAVI), global longitudinal strain average (GLS avg), end-diastolic volume (LVEDV).*

h
*Included measurement of the inferior vena cava (IVC) diameter at expiration and at maximum inspiration, collapsibility index of the IVC, assessment of sonography criteria of non-alcoholic fatty liver disease (NAFLD).*

i
*Included measurement of the muscle thickness ulna for the estimation of skeletal body mass in kg using muscle sonography (calculated as Muscle thickness ulna in cm × body height in m × 4.89–9.15), assessment of the pennate angle in degrees and echogenicity of the vastus lateralis muscle in arbitrary units, quadriceps muscle thickness.*

j *Included active monitoring for dehydration, polyuria, nocturia, urogenital infections, (euglycemic) diabetic ketoacidosis*.

The decision to employ submaximal exercise testing as the primary outcome was based on several factors. First, the 6MWT is an inexpensive, efficient, safe and a well-tolerated method of assessing the functional exercise capacity of patients with ASCVD. It is widely used to follow the natural history of various diseases, and for measuring the response to medical interventions (40, 44, 45). Second, functional exercise capacity and mobility are composite of several factors targeted in rehabilitation programs in patients with established ASCVD and high cardiovascular risk with the goal of attaining physical activity levels in the community (13, 46–48). The 6MWT has been shown to correlate closely with physical performance levels in the community (49, 50) and to be strongly associated to clinical change and functional capacity following rehabilitation (51–53). The test reproduces the limitations of physical performance when undergoing activities of daily living such as dyspnea, fatigue, pain and weakness, while maximal aerobic capacity testing mainly measures the reserve capacity (thought to be barely tapped during daily activities) limited by exertion (54, 55). Third, evidence shows that the 6MWT is not associated with a relevant learning effect when repeated testing is performed in individuals with ASCVD (51, 56, 57). Fourth, minimal clinically important difference has been defined for the 6-MWT and helps determine whether a given change in the 6-MWT represents a clinically meaningful difference (58–60). Fifth, previous studies show that in patients with established ASCVD, poor physical performance measured with the 6-MWT is an independent predictor of survival and predicts risk of hospitalization, all-cause mortality, cardiovascular disease mortality, and mobility loss (44, 61–64). Together, these aspects mean the results of the primary outcomes of the PUSH should be indeed translatable to similar cohorts of patients with established ASCVD and high cardiovascular risk with or without a T2D comorbidity.

Furthermore, the duration of follow-up of 28 days was mainly based on a previous pilot study participants with similar comorbidities that showed that the SGLT2-inhibitor empagliflozin was associated with 1-month improvement in exercise capacity in T2D patients with symptomatic CHF measured amongst others using the 6-MWD and that this beneficial effect was also found for other surrogates of severity including quality of life measures and markers associated with congestive heart failure as measured in some of the secondary outcomes below (28).

#### Secondary outcomes

Secondary outcomes included surrogate variables related to or influencing physical performance measured as follows:

##### Transthoracic echocardiography parameters at rest

Main echocardiographic parameters such as left ventricular mass index (LVMI) in kg/m^2^, diastolic function (E/e' average), left atrial volume index (LAVI) in ml/m^2^, global longitudinal strain average (GLS avg) in %, doppler techniques used to measure end-diastolic volume (LVEDV) in ml, resting stroke volume (SV) in ml, left ventricular ejection fraction (LVEF) with datasets registered and stored on an Echo PAC software (GE Medical Systems Glattbrugg, Switzerland) for analysis offline by an independent cardiologist unaware of the treatment allocation using previously described guidelines and protocols (65–67).

It has been well-proven that physical performance correlates strongly with cardiac size (LV volumes, LV mass or whole heart volumes), both in athletic and non-athletic populations (68, 69). Likewise, there is a strong correlation between resting cardiac geometry measures (LV mass, LVEDV) and exercise capacity in individuals with T2D (6). And although these previous studies could not demonstrate a correlation between LVEF and exercise capacity in individuals, the PUSH is designed to explore early changes in newer echocardiographic measures of subclinical LV systolic dysfunction in the presence of a normal ejection fraction such as global longitudinal strain average [GLS avg] (Figure 2) (70).

**Figure 2 F2:**
[figure not shown]
Global longitudinal strain average (GLS avg; here −17.2 %) as measured by a blinded cardiologist using images stored on an Echo PAC software.

##### Fatigue

Self-reported fatigue (continuous) and grade of fatigue severity (categorical) were measured using the Fatigue Scale for Motor and Cognitive function (FSMC) as previously described (71). In brief, the assessment is a patient-reported outcome measure (PROM) with a generic tool that measures a variety of aspects of fatigue. It employs a Likert-type 5-point scale ranging from “does not apply at all” to “applies completely” producing a score between 1 and 5 for each scored question. For the general scale, the minimum value is 20 (no general fatigue at all) and the maximum value is 100 (very severe general fatigue). Besides distinguishing between physical and cognitive fatigue, this scale offers a subdivision into different grades of fatigue severity with a cut-off value of ≥63 considered as severe, ≥53–62 moderate and ≥43–52 mild general fatigue (71, 72).

Independent of care providers, diagnosis upon admission or current treatment, the standardized and validated questionnaires are completed by patients in most rehabilitation centers in Switzerland to ascertain perceptions of their fatigue status and severity, perceived level of general as well as physical and cognitive impairment.

##### Grip-strength

Hand grip strength in kg measured using a JAMAR™ hand dynamometer recorded as the average of three measurements of the dominant hand in the neutral position. All participants performed the test upon admission and at discharge at the occupational therapy department, in the morning, on the same dynamometer and supervised by the same assessors blinded to patient medication.

Prior research showed grip strength is inversely associated with cardiovascular and all-cause mortality events especially in individuals with T2D (73–77).

##### Peak-expiratory-flow-rate

Peak expiratory flow rate in L/minute registered as the best of 3 attempts using a non-digital vitalograph™ peak flow meter (Vitalograph GmbH Hamburg, Germany) was measured during the clinical visits by treating rehabilitation physicians as a measure of pulmonary function and expiratory muscle strength.

To produce accurate measurements, assessors provided explanations and demonstrated the measurement to the participants so that they could fully understand the procedure before the measurements were performed.

The peak expiratory flow rate, in the absence of obstructive lung disease, has been shown in previous studies to have a strong correlation with expiratory muscle strength which is equally closely associated to hand grip strength (78, 79). Furthermore, in older adults physical performance has been shown to be more strongly associated with respiratory muscle mass than total skeletal muscle mass (80).

##### Body-mass-index

Body mass index (BMI) in kg/m^2^ measured as weight (kg) divided by measured height (m) squared. Weight and height were measured upon admission by blinded certified nurses and physiotherapists, respectively, and entered into patient records. During stay, weight was controlled at regular intervals in the morning before breakfast during the clinical visits by blinded nurses.

BMI is a crude adiposity indicator with higher BMI being an independent predictor of higher mortality risk in the general population (76, 77). On the other hand, many large cohort studies of individuals with T2D and high BMI suggest higher BMI to be a protective factor for all-cause mortality, a phenomenon described as the “obesity paradox” (81–83). Consequently, in interventions inducing weight reduction in individuals with T2D, such as regular exercise training in rehabilitation in combination with diet and SGLT2 is, lifestyle changes focussed around improving physical performance are recommended to alleviate the potential risk of BMI reduction and cardiovascular mortality (84, 85).

##### Muscle-mass

Estimated appendicular skeletal muscle mass (ASM) in kg using the previously described Baumgartner equation [ASM = 0.2487 (weight) + 0.0483 (height)−0.1584 (hip circumference) + 0.0732 (Hand grip strength) +2.5843 (SEX) + 5.8828] (86), and muscle sonography [ASM = 4.89 × Muscle thickness-forearm (ulna) × Height (m)−9.15] (87–89). Hip circumference is measured during the clinical examination by treating rehabilitation physicians at the level of the widest protrusion of the buttocks with the patient standing erect and feet together. Muscle thickness of the forearm is measured at the anterior forearm at 30 % proximal between the styloid process and the head of the radius by a single trained and certified sonographer using a GE Vivid S70 N R2 (GE Medical Systems, Switzerland) with a 9L-D 2.4–10-MHz linear array transducer (Figure 3).

**Figure 3 F3:**
[figure not shown]
Muscle thickness ulna right forearm (here 3.85 cm).

Not only is there a strong relation between muscle mass and physical performance (90), but also muscle mass as a measure of muscle quantity has been shown to have a strong correlation with ASCVD mortality with high muscle/low fat mass individuals having a lower risk of ASCVD and total mortality (91–93).

##### Muscle-quality

Muscle echogenicity of the vastus lateralis muscle on B-Mode ultrasound imaging obtained by a single trained and certified sonographer using a GE Vivid S70 N R2 (GE Medical Systems, Switzerland) with a 9L-D 2.4–10-MHz linear array transducer with duplicate assessment of outcomes using Image J software [Wayne Rasband, National Institute of Mental Health (NIH)] by an independent sonographer unaware of the treatment allocation following previously described protocols (94–96) as shown in Figure 4.

**Figure 4 F4:**
[figure not shown]
Measurement of echogenicity of the right vastus lateralis muscle using Image J software.

Muscle strength and physical performance are affected by not only muscle mass but also muscle quality which could be measured by echogenicity in ultrasound imaging (97, 98). Echogenicity reflects muscle quality, since non-contractile tissue associated with myosteatosis shows hyper-echogenicity (Figure 4) (98). Furthermore, individuals with T2D have been shown to have a an impaired microvascular blood flow in the muscles which could partially explain the impaired physical performance (99, 100).

To check for inter-rater and intra-rater reproducibility of the ultrasound measurements, especially when older individuals are examined, regular in-study reliability assessments (ICC) were conducted randomly on 30 patients of the PUSH study. For the ICC evaluation, measurements were repeated 3 times for each participant. The measured data shall be analyzed using a single-measurement, absolute-agreement, 2-way mixed-effects model and reported as ICC with 95% confident interval. Based on the ICC results, the measurements shall be classified according to the subgroups defined by Landis and Koch, in which ICC values below 0.00 are considered poor reliability, 0.00–0.20 slight reliability, 0.21–0.40 fair reliability, 0.41–0.60 moderate reliability, 0.61–0.80 substantial reliability, and 0.81–1.00 almost perfect reliability (101).

##### Functional-status

Functional independence measure (FIM™) as registered by blinded certified nursing staff. The FIM™ measures functional status, independent of diagnosis, using an 18-item, seven-level, ordinal scale intended to be sensitive to changes over the course of a comprehensive inpatient rehabilitation program (102).

The change in the FIM score has been shown to strongly correlate with long-term mortality in patients with CeVD admitted for rehabilitation (103).

##### Walking-aids

Use of walking aids (categorical) as documented by blinded physical therapists. As a measure of functional independence and balance, change in the need and use of walking aids is also a proxy measurement of change in physical performance in individuals with T2D (104, 105).

##### N-terminal-pro-brain-natriuretic-peptide

Fasting blood samples (serum or plasma as appropriate) are evaluated for circulating levels of N-terminal pro-brain natriuretic peptide (NT-pro-BNP) in ng/L [1 Nanogram per liter (ng/l) = 1 Picogram per milliliter (pg/ml)] measured by laboratory technicians unaware of study group allocation.

In patients with ASCVD, NT-pro-BNP levels have been shown to predict physical performance and cardiovascular events (106–109).

##### Anthropometric-indices

Anthropometry comprising of mean waist and hip circumferences in cm, waist-to-height, and waist-to-hip ratios. Waist circumference was measured during the clinical examination by treating rehabilitation physicians at the level of the umbilicus with the patient standing erect and feet together.Waist circumference has been demonstrated to be a modifiable factor associated with post-rehabilitation physical performance and function (110). Additionally, both waist-to-height and waist-to-hip ratios have been associated with cardiovascular events (111–113).

##### Parameters-of-muscle-physiology

Fasting blood samples (serum or plasma as appropriate) evaluated for biomarkers of muscle response to training including creatinine kinase (CK) in U/L, lactate dehydrogenase (LDH) in U/L (114), and biomarkers likely influencing both musculoskeletal function and cardiovascular disease including serum magnesium (115, 116) in mmol/L, serum ionized calcium and serum vitamin D levels (117).

##### Other-biomarkers-associated-with-fatigue

Fasting blood samples (serum or plasma as appropriate) were evaluated for biomarkers of iron deficiency including serum ferritin in μg/L, transferrin saturation (TSAT) in % (118).

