#### Data analyses

Demographic data will be examined using independent-samples *t*-tests and Fisher's exact tests for dichotomous variables. Independent-samples *t*-tests and repeated-measures ANOVAs will be employed to compare changes in physical performance after 4 weeks. Differences between primary and secondary outcome variables after 4 weeks will also analyzed by linear mixed-effects models (LMMs). The time factor for the model will be set at baseline and week 4. The models will include model-based adjustments for baseline characteristics influencing physical performance in such cohorts: (1) age, sex, BMI, waist circumference, diabetes duration and history of cardiovascular disease.

To minimize the bias that could result from participants in the 3 groups having highly variable duration of stay, the prospective analyses will be performed on a modified intention-to-treat and per protocol basis. The modified intention-to-treat population will be defined as participants who have been categorized to a study group and have at least one follow-up measurement of the primary outcomes, regardless of treatment adherence or duration of stay. The “last observation carry-forward method” will be used in the absence of complete follow-up data. For “per protocol” analysis, only those participants who have follow-up measurements after a minimum treatment duration or length of stay of ≥20 days will be included.

Sensitivity analyses will be performed to account for potentially non-ignorable missing data due to dropout as well as the possible impact of other potentially influential variables. A Bonferroni correction will be applied to the LMM analyses of the primary and secondary outcomes.

Pre-specified subgroup analyses will be conducted; these will include subgroups defined according to the various entities of ASCVD, gender, age groups, and other factors.

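### Five biomarker outcomes are compared between non-randomized groups without accounting for the recorded iron, magnesium, calcium and vitamin D substitution

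*Protocol article*

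**What the plan says.** All references are to the protocol article.

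- **Status of the markers.** The section Secondary outcomes opens with "Secondary outcomes included surrogate variables related to or influencing physical performance measured as follows". Under Other-biomarkers-associated-with-fatigue, fasting samples "were evaluated for biomarkers of iron deficiency including serum ferritin", and TSAT is listed with it. Under Parameters-of-muscle-physiology come "biomarkers likely influencing both musculoskeletal function and cardiovascular disease including serum magnesium" and, in the same list, "in mmol/L, serum ionized calcium and serum vitamin D levels".
- **Substitution.** Footnote c of Table 1 includes "vitamin D, iron, calcium, and magnesium substitution" in the medication status. Table 1 marks that item at baseline, week 2 and week 4; the text above the table makes week 2 optional.
- **Analysis.** Data analyses puts primary and secondary outcomes into linear mixed-effects models with time at baseline and week 4. The adjustment set is "age, sex, BMI, waist circumference, diabetes duration and history of cardiovascular disease". The two analysis sets are a modified intention-to-treat set and a per-protocol set defined by length of stay.
- **Nearest provision.** The same section promises sensitivity analyses for missing data and for further influential variables, without naming any.

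**The concern.** Each of the five markers measures a substance that can be supplied directly by a treatment recorded in the same study. A patient who starts iron or vitamin D after admission may show a rise that owes nothing to exercise, glycemic control or an SGLT2 inhibitor. The groups are formed by fasting glucose and diabetes status, so nothing in the design balances prescribing between them.

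Two passages make this more than abstract. Under Study group categories, HbA1c is rejected as the measure of glycemic control because some participants will have had bleeding or transfusion before rehabilitation. The authors therefore expect patients whose iron status may be disturbed, yet ferritin and TSAT have no matching safeguard. Note a to Table 1 also allows baseline values to be taken from the preceding hospital stay, so substitution begun between that sample and admission can enter the measured change.

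At stake is the reading of a group difference in these markers as a metabolic or muscle response when it may be a difference in prescribing.

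**Working it through.** The plan states no figure on this point, so there is none to reproduce. The check has two parts.

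**1. Passages side by side**

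| Outcome | Matching substitution in Table 1, footnote c | In the model covariates? |
|---|---|---|
| Ferritin | Iron | No |
| TSAT | Iron | No |
| Magnesium | Magnesium | No |
| Ionized calcium | Calcium | No |
| Vitamin D | Vitamin D | No |

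The stated list has six items, none of them a co-medication. Neither analysis set is defined by substitution, and no other handling of it is stated.

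**2. How the bias depends on prescribing (illustration only)**

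Input from the article: 130 participants per group and two-sided alpha of 5% (Sample size). Assumed, because the article gives neither: the difference between two groups in the share substituted (d), from 5 to 30 percentage points, and the effect of substitution on the analysed change (e), from 0.5 to 1.5 SD.

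- Bias in the group contrast, in SD units: b = d × e.
- Standard error of the contrast: SE = √(2/130) = 0.124.
- Probability of a nominally significant result with no true group effect: 1 − Φ(1.96 − b/SE) + Φ(−1.96 − b/SE).

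Worked case, d = 0.10 and e = 1: b = 0.10; b/SE = 0.806; 1 − Φ(1.154) = 12.4%; Φ(−2.766) = 0.3%; total 12.7%.

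| d | e = 0.5 SD | e = 1.0 SD | e = 1.5 SD |
|---|---|---|---|
| 5 points | b = 0.025; 5.5% | b = 0.05; 6.9% | b = 0.075; 9.3% |
| 10 points | b = 0.05; 6.9% | b = 0.10; 12.7% | b = 0.15; 22.7% |
| 20 points | b = 0.10; 12.7% | b = 0.20; 36.4% | b = 0.30; 67.7% |
| 30 points | b = 0.15; 22.7% | b = 0.30; 67.7% | b = 0.45; 95.2% |

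With d = 0 the bias is zero and the rate is the nominal 5%. The planned Bonferroni correction would lower the percentages but leaves b unchanged. The table shows a dependence; it does not estimate what happened in this study.

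**The case against.** The strongest reply is that this is detail for the full analysis plan. A condensed article need not say how co-medication is handled for five laboratory markers among many secondary outcomes; the sensitivity clause leaves room for it, and the data are collected. This stands in part. No contradiction is shown, and the full plan may deal with it. But the article does fix a covariate list and two analysis sets and applies them to all outcomes, and the point is that this stated choice does not suit these five markers. The sensitivity clause commits to nothing about substitution.

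A second reply is that the size is wholly assumed. That stands. The article gives no rates, no route of administration and no SD for any of the five markers. At the low end of the table the false-positive rate is practically nominal.

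A third reply is that the limitations in the Discussion already rule out causal conclusions. That softens the consequence but does not remove it, because an adjusted association with group would still be reported.

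A reader might go further and infer any of three things that the documents do not support:

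- **The five comparisons are in fact biased.** Nothing shows that substitution differs between groups.
- **The main findings are threatened.** The markers are secondary, and the walk-test outcomes do not depend on this point.
- **The main analysis should drop everyone who started or changed substitution.** Starting is a post-baseline decision, probably prompted by a low admission value and possibly related to the exposure. Excluding those patients would trade confounding for selection and would abandon the modified intention-to-treat principle, which keeps participants whatever their adherence or stay.

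**Conclusion.** The point holds in limited form. As written, the group comparison of ferritin, TSAT, magnesium, ionized calcium and vitamin D cannot separate a response to group or SGLT2 inhibitor from a difference in supplement prescribing, although the data to examine this are recorded. The size of any bias cannot be determined from the documents. Under the assumed ranges it runs from 0.025 to 0.45 SD, and it is zero if substitution is equal across groups. The conclusion rests on the stated covariate list being the one used for these markers. It is worth correcting because the remedy is cheap, but it concerns the interpretation of five secondary markers only.

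**What to change.** For these five markers:

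1. Keep the all-participant modified intention-to-treat analysis as the main one.
2. Add baseline use of the matching substitution as a covariate. Because the models take baseline and week 4 as time points, enter it with its interaction with time; a main effect alone would shift both time points equally and leave the change largely unadjusted.
3. Report, per group, how many started or changed the matching substitution between baseline and the follow-up measurement analysed.
4. Pre-specify beside the main result a sensitivity analysis restricted to participants with unchanged substitution.
5. Interpret a group difference as a metabolic or muscle response only if the two analyses agree, and even then as an association.

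The cost is a few sentences in the analysis plan and no new data. The article describes the analyses as still to be done, so the change can precede them. The downsides are that the restricted analysis has fewer participants and selects on a post-baseline event, which is why it should be supportive and not primary. Because week 2 is optional, a substitution begun and stopped between baseline and week 4 may also be missed.
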